# Randomized trial comparing low-pressure versus standard-pressure pneumoperitoneum in laparoscopic colectomy: PAROS trial

**DOI:** 10.1186/s13063-020-4140-7

**Published:** 2020-02-22

**Keywords:** Laparoscopy, Colectomy, Low-pressure pneumoperitoneum

## Abstract

**Background:**

Laparoscopy, by its minimally invasive nature, has revolutionized digestive and particularly colorectal surgery by decreasing post-operative pain, morbidity, and length of hospital stay. In this trial, we aim to assess whether low pressure in laparoscopic colonic surgery (7 mm Hg instead of 12 mm Hg) could further reduce pain, analgesic consumption, and morbidity, resulting in a shorter hospital stay.

**Methods and analysis:**

The PAROS trial is a phase III, double-blind, randomized controlled trial. We aim to recruit 138 patients undergoing laparoscopic colectomy. Participants will be randomly assigned to either a low-pressure group (7 mm Hg) or a standard-pressure group (12 mm Hg). The primary outcome will be a comparison of length of hospital stay between the two groups. Secondary outcomes will compare post-operative pain, consumption of analgesics, morbidity within 30 days, technical and oncological quality of the surgical procedure, time to passage of flatus and stool, and ambulation. All adverse events will be recorded. Analysis will be performed on an intention-to-treat basis.

**Trial registration:**

This research received the approval from the Committee for the Protection of Persons and was the subject of information to the ANSM. This search is saved in the ID-RCB database under registration number 2018-A03028–47. This research is retrospectively registered January 23, 2019, at http://clinicaltrials.gov/ed under the name “LaPAroscopic Low pRessure cOlorectal Surgery (PAROS)”. This trial is ongoing.

## Background

Laparoscopic colectomies are performed for two types of pathologies: colorectal cancers and benign diseases (Crohn’s disease, ulcerative colitis, diverticulitis, familial adenomatous polyposis, and non-resectable polyps in endoscopy). Currently, laparoscopy is performed for the large majority of digestive surgical procedures instead of laparotomy. The laparoscopic approach for colectomy has better short- and long-term results compared with laparotomy in terms of morbidity, mortality, quality of resection, recurrence, and survival in cancer [1–7]. In the majority of the studies, the authors report a significant decrease in the length of hospital stay in laparoscopic patients. More recently, in a French cohort study of 84,000 patients, it was demonstrated that laparoscopy was the only factor decreasing post-operative mortality [8].

Despite all the apparent advantages of laparoscopy because of its minimal invasiveness (reduction of post-operative pain, improved patient satisfaction, improvement of aesthetic results, and decrease in hospital length of stay), the creation of a pneumoperitoneum has an impact on the cardiovascular and respiratory physiology and has certain limits such as the instability of the pneumoperitoneum, compromised visibility during bleeding, evacuation of smokes, and post-operative shoulder tip pain. Adverse events due to intra-abdominal insufflation of carbon dioxide (CO_2_) are now evaluated, so that their occurrence does not impact the benefits sought by choosing laparoscopic methods [9]. In addition to pain caused by phrenic irritation, residual gas, and abdominal wall stretching, the hemodynamic (reduced venous return and cardiac output and increased peripheral vascular resistance and blood pressure) and metabolic effects of pneumoperitoneum are well-recognized issues [9–14]. From a respiratory standpoint, it reduces lung volume, increases pulmonary resistance, decreases pulmonary compliance, and increases the risk of barotrauma. There is also a possible alteration of renal function. Owing to the absorption of CO_2_, the hypercapnia thus induced can lead to a stimulation of the sympathetic nervous system and increase the plasmatic catecholamines. Owing to these potential effects, European endoscopic guidelines recommend insufflation with the minimum pressure which allows maintenance of sufficient exposure [10]. However, there are no patient outcome data in the literature comparing low- versus standard-pressure pneumoperitoneum in laparoscopic colectomy.

## Objectives

The primary objective is to determine whether low-pressure (7 mm Hg) instead of standard-pressure (12 mm Hg) pneumoperitoneum for patients undergoing laparoscopic colonic resection results in a reduced length of hospital stay of at least 1 day. The secondary objectives are the comparison between groups of post-operative pain, analgesics consumption, 30-day post-operative morbidity, operative time, bleeding, quality of visibility during intervention, conversion rate, perioperative cardiovascular and respiratory function, time to passage of flatus and stool, time to sitting out and mobilizing, and quality of oncological resection (lymph node dissection and curative resection).

## Methods and analysis

### Study design

This is a phase III hospital-based, prospective, randomized, controlled, single-center trial.

### Study population

The patients will be recruited by colorectal surgeons of the Department of Digestive Surgery of the Magellan Medico-Surgical Centre (University Hospital of Bordeaux, France). Patients scheduled for elective colonic laparoscopic surgery for either cancer or benign colonic pathologies (Crohn’s disease, chronic ulcerative colitis, diverticulosis, familial adenomatous polyposis, non-resectable colonic polyps in endoscopy, or other indication) will be assessed for suitability for inclusion.

### Inclusion criteria

Inclusion criteria will be: patients undergoing a right or left colectomy for a malignant or benign pathology, planned laparoscopic procedure, and age of 18 years or older. Following counselling with a member of the research team and provision of written patient information relating to the study prospective, signed informed consent will be obtained from each patient before inclusion.

### Exclusion criteria

Exclusion criteria include: non-laparoscopic procedure, transverse or total colectomy or other procedure performed simultaneously with colonic surgery (except appendectomy or liver biopsy), emergency surgery, surgery for pelvic sepsis, pregnant woman, likely to be or breastfeeding, any patient incapable of providing informed consent, and those unable to commit to the medical follow-up of the study for geographical, social, or psychological reasons.

### Consent and randomization

During the pre-inclusion visit, the investigator will inform the participant and answer all questions regarding the purpose, nature of, foreseeable risks, and the expected benefits of the clinical trial. The investigator is responsible for obtaining informed consent from the participant. An original copy of the information note and signed consent will be given to the patient. The other original copy will be retained by the investigator as part of the study documents in an area inaccessible to third parties. After the written consent of the patient is obtained, randomization will take place the day before or the day of the procedure but at the latest before the incision. When an investigator (“operator” surgeon) wishes to perform the randomization/inclusion after verifying the eligibility of the participant, they will send a randomization application document to the statistician of the study, who will send back a patient number (of three digits corresponding to the inclusion rank), an anonymous letter code (four letters), and the result of the randomization arm, namely group A (experimental): insufflation at low pressure (5–7 mm Hg) or group B (control): insufflation at standard pressure (12–15 mm Hg). The two groups will be balanced with a ratio of 1:1. Randomization will be performed by using the following method: for each subject entering the study, a number K between 0 and 9 will be drawn randomly from Excel. The subject will be assigned to the control group if K is 0 or even or to the “low pressure” group if K is odd. Simple randomization does not necessarily lead to homogenous groups. However, a deviation of less than 20% should have little effect on power loss, and the groups should equilibrate with larger sample sizes (more than 50).

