### Sample size

The calculation of the number of subjects required is based on the primary endpoint, which is a decrease in hospital length of stay of at least 1 day in patients operated on laparoscopically for malignant or benign colonic pathology using a low-pressure pneumoperitoneum with the medical insufflation device AirSeal®. The activity of the Colorectal Unit of the Magellan Medico-Surgical Centre was 170 colonic laparoscopic resections in 2017, and the average hospital stay of patients in this control arm would be 5 ± 2 days based on available data. As such, in unilateral formulation, to show a difference (1 day) with an alpha risk of 5% and a power of 90%, there should be 69 patients recruited per group, resulting in a total of 138 patients.

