### Statistical analysis

The main analysis will focus on all randomly assigned patients (intention-to-treat analysis). The alpha risk is 5% and the power is 90%. Given the main variables studied, there will be no missing data for analysis of the primary outcome. The descriptive statistical analysis will include the following for each quantitative parameter at each time: average, standard deviation, minimum, maximum, median and quartiles, and number of missing values. The categorical variables will be expressed by the frequency of distribution and the associated 95% bilateral confidence intervals. For the primary endpoint, which is theoretical length of hospital stay, the two groups will be compared by using Student’s *t* test if, as suggested by a preliminary study, the distribution of the variable does not deviate significantly from a Gaussian distribution; otherwise, a Mann–Whitney test will be used. For the secondary endpoints, the categorical criteria will be analyzed by using a chi-squared test. In the event that the chi-squared validity criteria are not verified, an exact probability test will be used. Quantitative secondary criteria will be compared by *t* test or Mann–Whitney according to their distribution in the sample considered. All tests will be bilateral at risk of the first species set at 5%. The analysis will be performed by using IBM SPSS Statistics, version 20 software (IBM, Armonk, NY, USA).

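### Simple randomisation followed by an unadjusted primary test is valid, but forgoes a modest, cheap precision gain from colectomy side and indication

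*Protocol article*

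**What the plan says.** Protocol article, Consent and randomization: a digit from 0 to 9 is drawn for each patient; zero or even means control, odd means low pressure. There are no blocks and no strata. The section concedes: "Simple randomization does not necessarily lead to homogenous groups". Its defence is that a deviation under 20% costs little power and that the groups should even out once the sample passes 50.

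Protocol article, Inclusion criteria: the population is "patients undergoing a right or left colectomy for a malignant or benign pathology". Both features are settled when the patient is included.

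Protocol article, Statistical analysis: "For the primary endpoint, which is theoretical length of hospital stay, the two groups will be compared" by Student's t test, or by Mann–Whitney if stay is not close to Gaussian. No covariate enters. The same section adds: "All tests will be bilateral at risk of the first species set at 5"%.

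Protocol article, Sample size: "the average hospital stay of patients in this control arm would be 5 ± 2 days based on available data"; the calculation is "in unilateral formulation, to show a difference (1 day") "with an alpha risk of 5% and a power of 90"%, and concludes that "there should be 69 patients recruited per group, resulting in a total of 138 patients".

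**The concern.** The section on randomisation raises the homogeneity of the groups, but the argument it offers is about how much power an uneven split costs. It proposes nothing for case mix, and the analysis section does not return to it. If side or indication influences stay, two things follow. The variation they explain remains in the error term of the primary test, so the confidence interval is wider than it need be. And if the arms happen to differ in these factors, the estimate of that one trial is displaced by a known, correctable amount. A prespecified adjustment deals with both. If none is prespecified and the baseline table shows an imbalance, any adjustment chosen afterwards will look data-driven.

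**Working it through.** **Inputs from the protocol article.** Difference 1 day, SD 2 days, alpha 5%, target power 90%, 69 per group, 1:1 allocation, one-sided sizing (Sample size; Consent and randomization); two-sided tests (Statistical analysis).

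**Inputs not in the documents (assumed).** The share R² of the variance of stay explained by side and indication; how common each factor is; how many days each is worth.

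**1. The plan's own figure.** n per group = 2 × [SD × (z₁₋α + z₀.₉₀) / difference]² = 2 × [2 × (1.645 + 1.282) / 1]² = 68.5, so 69. The figure reproduces one-sided. The two-sided version of the same formula gives 85. With 69 per group, power is 90.2% one-sided and 83.6% two-sided by the normal approximation (89.9% and 83.0% by the t distribution).

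**2. Unequal group sizes.** Under simple randomisation of 138 patients, the 95% range of the split is 58/80 to 80/58. Two-sided power (normal approximation) is 82.6% at 58/80 against 83.6% at 69/69. The chance that the groups differ by 20% or more of the total is about 2%. On group size the article's defence is correct.

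**3. Chance imbalance in one factor.** For a factor with prevalence p, the SD of the between-arm difference in proportions is √[2p(1 − p)/69].
- p = 0.50: SD 0.085; chance of a gap of 10 points or more 24%, of 15 points or more 8%.
- p = 0.30: SD 0.078; the same chances are 20% and 5%.

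**4. What an imbalance does to the estimate.** Displacement = gap × effect of the factor on stay. For a factor worth 1 day, a 10-point gap gives 0.10 × 1 = 0.10 day. A gap at the 95% limit (1.96 × SD, or 15 to 17 points) gives 0.15 to 0.17 day. The standard error of the unadjusted difference is 2 × √(2/69) = 0.34 day.

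**5. Gain in power from adjustment.** The residual SD becomes 2 × √(1 − R²). Two-sided power with 69 per group:

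| R² (assumed) | Residual SD | Power, normal | Power, t distribution |
|---|---|---|---|
| 0 | 2.000 | 83.6% | 83.0% |
| 0.02 | 1.980 | 84.3% | 83.8% |
| 0.05 | 1.949 | 85.4% | 84.9% |
| 0.10 | 1.897 | 87.2% | 86.7% |
| 0.20 | 1.789 | 90.7% | 90.3% |

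By the normal approximation, 90% needs R² = 1 − 69 / [8 × (1.960 + 1.282)²] = 0.18 (0.19 by the t distribution).

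**6. What size of factor that implies.** For one binary factor worth d days, R² = p(1 − p)d²/4. With p = 0.50, d = 0.5 gives 0.016 and d = 1 gives 0.0625, so a gain of under 1 point and of about 2 points. R² = 0.18 requires d = √(0.18/0.0625) = 1.7 days, or two independent factors of 1.2 days each.

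**7. Validity of the planned test.** In 20,000 simulated trials per scenario with simple randomisation, the unadjusted t test rejected a true null in 4.9% to 5.1% of trials. Simulated power, unadjusted against adjusted, was 83.2% and 84.8% (R² = 0.05), 82.7% and 85.9% (0.10), and 83.0% and 89.9% (0.20).

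**The case against.** The strongest reply is that nothing here is an error. A two-group test after simple randomisation keeps its type I error, and its standard error already allows for chance imbalance. That stands. A reader might infer that the primary result will be biased; the documents do not support this, because chance imbalance averages to zero over randomisations and the simulated error rate stays at 5%.

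A reader might also infer that missing adjustment is why power is near 83% rather than 90%, or that adjusting would restore it. Neither follows. The shortfall comes from sizing the trial one-sided while all tests are two-sided. Closing it by adjustment alone would need factors stronger than the 1-day treatment effect sought, and the article gives neither their strength nor their frequency.

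It can further be said that the remark about evening out beyond 50 patients covers composition as well as size, and that exclusions and standardised care narrow the case mix. The wording allows that reading, and these features may make R² small. Even so, with 69 per arm a 10-point gap in a common factor remains a 20% to 24% event.

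Finally, an analysis plan that is not shown may contain adjusted supportive analyses, and their absence from the article is no fault. The primary test, however, is stated in the article, and it is unadjusted.

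**Conclusion.** The point holds as a matter of efficiency, not of validity. The article fixes an unadjusted primary comparison after unstratified randomisation and leaves unused two baseline factors that every patient has. The likely gain is small: about 1, 2 or 4 points of two-sided power if the factors explain 2%, 5% or 10% of the variance in stay. The displacement from a 10-point imbalance in a 1-day factor is 0.10 day, under a third of the standard error (0.10/0.34 = 0.29). All of this rests on assumed R², prevalence and effect sizes. The change is still worth making, since its price is low even if the factors turn out to predict little.

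**What to change.** Before unblinding, prespecify as the primary analysis a linear model of theoretical length of stay on arm, side (right/left) and indication (malignant/benign), with indication taken as recorded at inclusion. Report the adjusted mean difference in days with its 95% confidence interval, which answers the 1-day objective directly. Stay is likely to be skewed and the present plan has a Mann–Whitney fallback for that case, so use robust or bootstrap standard errors in the model and keep the planned t or Mann–Whitney comparison as supportive. The randomisation need not change.

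The cost is a small but real amendment to the primary analysis of an ongoing trial, plus two degrees of freedom out of 136. No extra patients or data are needed. Reconcile the one-sided sample size with the two-sided tests separately; adjustment does not replace that correction.

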### Blinding

The study will be double-blind. In order to minimize the self-assessment bias of post-operative pain, the patient will not know the group he or she belongs to. The surgeon who decides to discharge the patient from the hospital and who evaluates the primary and secondary endpoints (the “evaluator” surgeon) will not be the “operator” surgeon.

### Intervention

The “operator” surgeon is the surgeon who performs the procedure. The team is made up of six different surgeons, each with their own patients and using the same surgical techniques. The “evaluator” surgeon is the surgeon who validates the patient’s discharge according to predefined and objective criteria. The operating surgeon does not validate the discharge of his own patients. The patient also ignores the arm in which he or she was randomly assigned. The results of randomization are known only by the department’s clinical researchers and kept in a password-protected Excel database. The result is communicated only to the “operator” surgeon on the day of the operation. He knows the randomization arm because it is up to him to adjust the insufflation pressure during the procedure. On day 0, the “operator” surgeon performs a laparoscopic colectomy by using the AirSeal® medical device (ConMed, Utica, NY, USA) and adjusts the insufflation pressure in accordance with the results of the randomization: low-pressure insufflation at 7 mm Hg or standard-pressure insufflation at 12 mm Hg. Different anesthesia and analgesia may affect the secondary outcomes, post-operative pain scores, consumption of analgesics, and recovery time. This is why the anesthetic and analgesic protocol are standardized in both groups and explained in schematic form in the Appendix. The intra-operative protocol starts before the introduction of the trocar: we infiltrate the orifices with 2% naropeine. Then the patient receives a continuous infusion of ultiva, ketamine (0.3 mg/kg as a loading dose and then 0.15 mg/kg per hour until the end of the surgery), and xylocaine (continuous dose of 1.0 mg/kg, stopped 1 h before the end of the surgery). One hour before the end of the surgery, we perform a morphine bolus of 0.1 mg/kg, 50 mg of profenid, and 1000 mg of paracetamol. In the post-operative care room, a morphine titration will be performed if necessary (the amount of morphine given is notified) and the patient receives 1000 mg of paracetamol again 1 h after the surgery is completed. In the post-operative period, the patient systematically receives 1000 mg of paracetamol every 6 h and 50 mg of profenid every 6 h for 48 h. The patient also receives 50 mg of topalgic only if needed and all doses are notified (maximum 8 per 24 h). Perioperative respiratory and cardiovascular management are also standardized. Cardiovascular data will include systolic blood pressure, diastolic blood pressure, mean arterial pressure, heart rate, cardiac index, stroke volume, and stroke volume variation. We also collect the volume of hydration and filling, balance of inputs and outputs, and total doses of ephedrine and noradrenaline (if needed). Respiratory data will include tidal volume, end-tidal CO_2_, respiratory frequency, peak pressure, peak pressure, plateau pressure, driving pressure, compliance (exhalation pressure at 0 and 8 mm Hg), exhalation volume (at 0 and 8 mm Hg), inspired fraction of O_2_, O_2_ saturation, and functional residual capacity. The aerosols are used only if necessary in case of obstructive pathology (asthma or chronic obstructive pulmonary disease). The aerosol used if necessary is Salbutamol (beta-2 mimetics). The degree of muscle relaxation is monitored throughout the interventions using the TOF (Train of Four): four short stimulations of 0.2-ms duration, spread over 2 s. It measures the ratio between the response of the fourth and first stimulation (T4/T1 ratio) or counts the number of responses (from 0 to 4). We measure the TOF via the response of the ulnar nerve (thumb adduction) by using a device located on each patient’s wrist. For all procedures, the TOF must be equal to 0. The post-operative mobilization of the patient and the gastrointestinal recovery will be carried out in accordance with the ERAS (Enhanced Recovery After Surgery) early rehabilitation protocol [15]. Criteria for discharge will be carried out by a surgeon different from the one who performed the operation (“evaluator surgeon”). The patient will be hospitalized for the post-operative period in the colorectal unit of Magellan Medico-Surgical Centre. The follow-up will be standardized regardless of the randomization arm. All inpatient and outpatient adverse events will be recorded and reported. As part of the standard care in our colorectal unit, all patients have a post-operative consultation at 30 days (+15 days maximum) Fig. 1.

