### Outcomes

The primary outcome is to determine whether low-pressure (7 mm Hg) instead of standard-pressure (12 mm Hg) pneumoperitoneum during laparoscopic colonic resection leads to a reduction of the length of hospital stay of at least 1 day. The theoretical discharge date is the date of medical discharge of the patient, evaluated daily between 7 and 8 a.m., in accordance with predefined criteria, which are no pain requiring the use of analgesics more than stage 2, no nausea or vomiting, no fever of more than 38 °C, resumption of a normal diet, transit (passage of flatus/stool), patient mobilization, and patient acceptance. The real discharge date is the date of discharge including a possible continuation of hospitalization for non-medical reasons (i.e., waiting for convalescent home, personal suitability of the patient).

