Secondary outcomes are to determine how low-pressure pneumoperitoneum (7 mm Hg) influences: patient's post-operative pain (visual analogue scale after 2, 4, 8, and 24 h after surgery), the consumption of level 1, 2, and 3 analgesics, the transit and gas recovery time (days), the time before first time sitting and walking, the evolution of the perioperative cardiovascular and respiratory parameters (arterial blood pressure, heart rate, cardiac output, vascular filling, driving pressure, arterial oxygen saturation [SAO_2_], and post-exercise circulatory occlusion [PECO]), the operating time (from incision to closing, in minutes), the amount of bleeding, the visual quality of the procedure, the laparoscopy conversion rate to normal pressure or laparotomy, ability to achievean R0 resection in cancer surgery, the number of lymph nodes on the specimen and the rate of medical and surgical complications during the first postoperative 30 days (according to the DINDO classification). It seemed important to us to select post-operative pain because it is one of the major factors influencing the patient’s length of stay and very interesting to know whether a lower insufflation pressure makes it possible to reduce pain related to abdominal distention on the one hand and scapular pain on the other hand, which is described as extremely frequent in most laparoscopic procedures. The amount of analgesics (level 1, 2 and 3) is an objective data wich allows us to evaluate pain, wich is a subjective data. In addition, regarding the number of deaths currently associated with chronic opioid use, it seemed that defining whether low pressure allows opioid savings in the post-operative period was a major objective. We also know that taking opioids increases the time before transit resumes and that this influences the length of stay.

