### Data management

The data will be collected daily by the investigators. For the intra-operative data (respiratory and cardiovascular components, bleeding, and need for catecholamines or aerosols), they will be collected prospectively and transmitted by the anesthesiologist following each procedure. The exposure will be evaluated just after the procedure by the “operator” surgeon. The visual analogic scale at 2, 4, 8, and 24 h as well as the time before gas, stool, sitting, and walking are reported prospectively on a document that follows the patient at each time. The total amount of analgesics will be calculated on the day of discharge. All information required by the protocol will be recorded on the patient’s study notebook and a second time on electronic notebooks, and an explanation will be provided for each missing data variable. The entry will be made in FileMaker 9.0 version 3 (database software) stored on the network of Bordeaux University Hospital, which guarantees the confidentiality and security of the data processing in accordance with the requirements of the CNIL Reference Methodology. In accordance with the legislation in force, persons having direct access to the source data will take all the necessary precautions to ensure the confidentiality of the data. During or at the end of the research, the data collected on the individuals who are suitable for this analysis will be anonymized prior. The Bordeaux University Hospital network benefits from a daily backup of its data. The database is also stored and archived under the responsibility of the investigator in the colorectal surgery department of the Haut-Leveque Hospital of the Bordeaux University Hospital. For database freezing, a version number and a date will be given to the database, which is kept in a format that no longer allows modifications. A freeze certificate of the database will be completed and sent to the sponsor (EN-RCL-601). Data transfers (sending and receiving) will be carried out in accordance with the CMG procedure. For security reasons, the data files are anonymized and transferred via the secure platform CIRRUS.

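### Scheduled level 1 analgesics are counted as evidence on pain: their total to discharge either follows length of stay or is nearly constant by design

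*Protocol article*

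**What the plan says.** Four parts of the protocol article bear on this.

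- **Intervention**, scheduled drugs: "the patient systematically receives 1000 mg of paracetamol every 6 h and 50 mg of profenid every 6 h for 48 h". Two other drugs depend on need. For the recovery room: "a morphine titration will be performed if necessary (the amount of morphine given is notified". For the ward: "The patient also receives 50 mg of topalgic only if needed and all doses are notified". Every patient also gets a fixed intra-operative morphine bolus of 0.1 mg/kg, with profenid and paracetamol, an hour before surgery ends, and paracetamol again an hour after it.
- **Outcomes**: consumption of level 1, 2 and 3 analgesics is a secondary outcome, justified thus: "The amount of analgesics (level 1, 2 and 3) is an objective data wich allows us to evaluate pain". The same paragraph makes opioid saving a major objective.
- **Data management**: "The total amount of analgesics will be calculated on the day of discharge". No other period and no daily rate is given.
- **Statistical analysis**: quantitative secondary criteria go to a t test or Mann–Whitney test, chosen "according to their distribution in the sample considered". All tests are two-sided at 5%.

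The article does not label drugs by level. I assume that level 1 means paracetamol and profenid.

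**The concern.** A dose that every patient receives at fixed times carries no information on that patient's pain. The article still includes level 1 in the amount from which pain is to be judged, and sums it at a point that itself depends on the arm if the intervention works.

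The dosing sentence can be read in two ways. If the 48 h limit applies to profenid only, paracetamol continues and its total counts days in hospital. If it applies to both drugs, almost everyone has the same total. The Appendix that sets out the regimen is not shown, so the text does not settle which holds. Neither reading turns scheduled doses into a pain measure.

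At stake is the meaning of a secondary result. The trial is designed to detect a shorter stay. If it succeeds and paracetamol runs to discharge, the level 1 total will usually fall as well. Under the stated rationale that fall would count as evidence of less pain, when it only restates the stay. As-needed topalgic totalled to discharge has a milder form of the problem, because the arm that stays longer has more days on which to take it.

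**Working it through.** **The plan's own figure.** Inputs from the Sample size section: difference 1 day, SD 2 days, one-sided 5%, power 90%. n = 2 × 2² × (1.645 + 1.282)² / 1² = 68.5, so 69 per group, as stated. With the two-sided test of the Statistical analysis section, power at 69 per group is about 0.83.

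**Reading A: paracetamol runs to discharge.** Assume surgery ends at noon and departure is at 08:00 on day D, so hours in hospital after surgery are h = 24D − 4. Doses of 1 g are one before the end of surgery, one at 1 h, then one every 6 h: 2 + floor((h − 1)/6) = 4D + 1.

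- D = 5: 21 doses (21 g). D = 4: 17 doses (17 g).
- The total is linear in D, so its standardised difference is that of the stay: (4 × 1)/(4 × 2) = 0.5.
- Analytic two-sided power for the level 1 comparison, with no pain effect: 0.83 at SD 2, 0.97 at SD 1.5, 0.65 at SD 2.5.
- Simulation (gamma stays rounded to whole days, control mean 5, SD 2, 69 per arm, all scheduled doses given):

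| Difference in stay | Significant by t test |
|---|---|
| 1 day | about 82% |
| 0.5 day | about 30% |
| none | about 5% |

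The Outcomes section separates theoretical from actual discharge: "The real discharge date is the date of discharge including a possible continuation of hospitalization for non-medical reasons". The Statistical analysis section uses the former: "For the primary endpoint, which is theoretical length of hospital stay". Scheduled doses would follow the actual stay. If 10–30% of patients in both arms stay 1–4 extra days for non-medical reasons (assumed), the 1-day figure falls to 0.76–0.69 by t test and 0.81–0.73 by Mann–Whitney. The total's correlation with theoretical stay falls from 1.00 to 0.85.

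**Reading B: 48 h limits both drugs.** The same count with h capped at 48 gives 2 + floor(47/6) = 9 doses for anyone who stays two days or more, and 5 for departure on day 1. Mean doses are 8.96 v 8.74 with gamma stays and 8.99 v 8.87 with lognormal stays, a gap of 0.1–0.2 g. The total is not immune to a significant result. In a gamma simulation with the cap, Mann–Whitney was significant in about 41% of trials at a 1-day difference, 6% at half a day and under 1% at none. That comes entirely from the few one-day stays, so it again reflects departure and not pain, and it depends on the assumed lower tail of the stay distribution.

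**As-needed topalgic totalled to discharge, equal daily need in both arms.** At an assumed constant 2 doses per day: 2 × 116/24 = 9.7 doses for a 5-day stay and 2 × 92/24 = 7.7 for 4 days. Simulated proportion of trials with a significant difference, for a 1-day difference in stay, mean starting rate 1–4 doses per day and between-patient CV 0.5 or 1.0 (all assumed):

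| Pattern of use | Total to discharge |
|---|---|
| Constant until discharge | 18–44% |
| Halves every 2 days | 9–20% |
| Halves daily | 7–9% |

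Over a fixed 0–48 h window the figure is 5–7%. In this model 8% v 24% of patients leave by the morning of day 2, nearly all missing only the last 4 h of the window.

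**The case against.** The best reply has five parts.

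- **The 82% is conditional.** It needs paracetamol to run to discharge, a full 1-day effect on stay and no effect on pain. The text may limit both drugs to 48 h, and the article itself regards pain as a major driver of stay, so that combination is an extreme case. This stands: 82% is the upper end of a range that starts at 5%.
- **The Data management sentence may say only when the sum is made, not what period it covers, and does not say which discharge date is meant.** That is possible. But it is the only period stated, and no choice of period makes scheduled doses respond to pain. The article states the schedule, the interpretation and the totalling itself, so this is a wrong rule and not detail left to a fuller document.
- **A reader might infer that the authors will present a level 1 difference on its own as less pain.** The article does not say so. It gives one rationale for all three levels and does not say how they will be combined or tested. What the text supports is narrower: level 1 is expressly part of what is said to evaluate pain.
- **A reader might infer that opioid totals to discharge are invalid.** They are not. Fewer days on opioids is a real saving and fits the stated aim. The total is only a poor measure of pain intensity, and if topalgic use falls quickly the distortion is close to nil.
- **It would be too strong to say that only topalgic and recovery-room morphine respond to pain.** The discharge criteria in the Outcomes section imply that analgesics above stage 2 can be used on the ward, and as-needed paracetamol after the schedule ends is not excluded. A single level 1 total would mix the latter with the scheduled doses.

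**Conclusion.** The point holds for the interpretation of the analgesic-consumption endpoint. Under either reading of the 48 h limit, the scheduled level 1 doses do not measure pain, although the Outcomes section includes them in an amount that is meant to. The size depends on the reading: with no pain effect, 5% to about 82% significance under reading A as the difference in stay goes from none to 1 day; a gap of 0.1–0.2 g under reading B, driven only by early departure. The topalgic effect runs from almost none to 18–44% and rests on assumed use patterns.

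The results also rest on level 1 meaning paracetamol and profenid, on full adherence to the schedule and on the planning values of 5 v 4 days with SD 2. The primary endpoint and the sample size are unaffected, and pain is measured directly by visual analogue scale, though only to 24 h. Nothing here supports a claim that the main result is biased. The wording is worth changing because the change is cheap and because consumption is the stated objective check on a subjective scale.

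**What to change.** - **Outcomes:** base the pain interpretation only on as-needed level 2 and level 3 doses: topalgic, titrated morphine and any rescue opioid given on the ward, without the fixed 0.1 mg/kg bolus. Report scheduled level 1 doses descriptively, as adherence to the schedule, and list any as-needed paracetamol separately.
- **Data management:** compare these as-needed doses over one window common to both arms, for example 0–48 h after the end of surgery, or by post-operative day if dose times are not recorded. For patients who leave earlier, count doses to departure and report their number per arm.
- **Opioid saving:** keep total opioid use to discharge as a separate comparison, with a statement that it depends on length of stay and is not read as pain intensity.

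The change works under either reading of the 48 h limit. It alters no dosing and needs no extra patients, only wording before the database is frozen. Topalgic doses and recovery-room morphine are already noted and data are collected daily, so doses can probably be placed at least by day. The article does not say that dose times are recorded, so an exact 48 h cut may need the drug charts of patients already included. The other cost is that later as-needed use no longer enters the pain comparison.
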